### Randomization

Participants are simple randomized in a 1:1:1 ratio using a computer-generated random allocation sequence, by a statistician not further involved in the study. Participants will be assigned in sequential order to the treatment groups. The randomization list will be kept strictly confidential.

### Blinding

Participants, the homeopathic doctor, the psychologist and the statistician will remain blinded to the identity of the three treatment groups until the end of the study. The psychologist will assess the severity of the symptoms and will keep the HRSD scores strictly confidential in a closed envelope at every follow-up until the end of the study.

### Sample size calculation

Sample size calculation was estimated using G*Power (available at the University of Düsseldorf: http://www.psycho.uni-duesseldorf.de/abteilungen/aap/gpower3/). The sample size calculation is based on a previous study protocol for a randomized controlled trial of homeopathy for depression published by Adler *et al.*[21]. We assumed that *verum* treatment is better than placebo by 2.7 ± 6.0 (mean ± standard deviation) HRSD score points after six weeks [21], corresponding to an effect size = 0.45 (largest difference between any two groups to be detected/expected within group standard deviation = diff/de). To detect an effect size = 0.45, in a three-group design (1:1:1), using F-Test, with a 5% risk of type 1 error (α) and 83% power, 63 patients per group are required considering also a 10% drop-out rate.

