### Statistical analysis

All patients under randomization will be included in the primary efficacy population (intention-to-treat population), regardless whether or not they adhered to the treatment protocol or provided complete data sets. Only patients who withdraw their consent to use their personal data will be excluded from the analysis. The flow of participants through the trial will be presented in a Consolidate Standards of Reporting Trials (CONSORT) diagram.

First, the three groups will be compared in order to verify that there are no significant differences among them at baseline to confirm they are comparable after randomization. Demographic characteristics will be summarized using means and standard deviation for continuous data (that is, age) and relative frequencies for qualitative data (that is, marital status, comorbidities). The baseline demographic characteristics among groups will be compared with the use of the chi square test or by one-way independent measures of analysis of variance (ANOVA) as required.

We will compare: (1) IHT versus placebo; (2) fluoxetine versus placebo; and (3) IHT versus fluoxetine. The main statistical analysis will compare primary and secondary outcome measurements among groups at weeks four and six. The primary outcome (change in mean HRSD score) and secondary outcomes (change in mean BDI and GS scores) among groups at baseline and weeks four and six, will be analyzed by one-way ANOVA to provide a statistical test of whether or not the means of the three groups are all equal. The statistically significant one-way ANOVA result (*P* <0.05) suggests rejecting the global null hypothesis H_0_ (that the means are the same across IHT, fluoxetine and placebo groups). The Bonferroni *post-hoc* test will be used to determine which means differ among the groups. Responder rates will be compared among the groups using the chi square test. Statistical significance will be set at *P* <0.05 level for all analysis. Missing data will be handled by sensitivity analysis.

All patients who received at least one dose of the study drugs will be considered in the safety analysis. Adverse events will be translated to Medical Dictionary for Regulatory Activities terms (MeDRa terms), quantified and compared among the groups using the chi square test. Homeopathic aggravation will be compared among the groups also using the chi square test.

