Gibbons *et al.* reported that patients in all age and antidepressant groups have significantly greater improvement relative to placebo controls; and fluoxetine has been proven to be efficacious for depression in adults after six weeks of treatment [38], so it is expected that the fluoxetine-arm will result in significant differences versus placebo in this study. However, Kirsch *et al.* reported that, at present, it is becoming more difficult to prove that antidepressants actually work better than placebo in moderate to severe depression. It also has to be taken into consideration that the antidepressant-placebo difference seems to be smaller in the trials with moderately depressed participants [13]. Therefore, a fluoxetine-arm will allow us to detect if in Mexican women in the climacteric stage with moderate to severe depression, the difference in HRSD score between fluoxetine and placebo is as small as it has been shown in some meta-analysis [13].

Otherwise, different scenarios can result if no significant differences between IHT and placebo groups are found. In classical homeopathy, recovery requires the prescription of the individualized remedy at the adequate potency and dosage, so this is an important factor to be taken into consideration during the trial process because results may be biased. A negative result could be due to a mistaken election of the remedy and not because the IHT is inefficacious. Follow-up duration is also important. The selection of a suitable, individualized homeopathic medicine will not always be accomplished during six weeks of treatment, especially under double-blind conditions [21]. It has not been proved that six weeks of IHT is enough time to find a clinically relevant response in climacteric women with depression. In routine homeopathic consultation, a patient may require more than six weeks to recover from depression. However, for ethical reasons a longer follow-up is not possible because of the placebo group. Furthermore, homeopathic prescriptions may need to be modified depending on a patient’s individual response after homeopathic treatment is initiated. Once again, this could be problematic under double-blind conditions.

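### The stated 83% power does not follow from the plan's own inputs: an effect of 0.45 SD on a three-group F-test with 63 per group gives at most about 74%

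*Protocol article*

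**What the plan says.** All inputs stand in the Sample size calculation section of the protocol article. Active treatment is assumed "better than placebo by 2.7 ± 6.0 (mean ± standard deviation) HRSD score points after six weeks", and this is described as "corresponding to an effect size = 0.45 (largest difference between any two groups to be detected/expected within group standard deviation = diff/de"). The test is named as "in a three-group design (1:1:1), using F-Test". The result is "with a 5% risk of type 1 error (α) and 83% power, 63 patients per group are required", and the same sentence says that a 10% drop-out rate is allowed for.

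Under Statistical analysis, the primary outcome goes to a one-way ANOVA at the 5% level. Three pairwise comparisons are then listed, and the Bonferroni post-hoc "test will be used to determine which means differ among the groups". The Aims section states the primary aim as those same comparisons: IHT against fluoxetine, IHT against placebo, and fluoxetine against placebo.

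The Discussion adds that "a fluoxetine-arm will allow us to detect if in Mexican women in the climacteric stage with moderate to severe depression" the fluoxetine-placebo difference is as small as in some meta-analyses. The Background gives 1.8 HRSD points from one such meta-analysis and a 3-point criterion for clinical significance.

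**The concern.** The effect size is defined as a standardised range, the largest difference divided by the SD. An F-test for three groups works on a different quantity, Cohen's f, and a range of 0.45 corresponds to an f of roughly half that or less. The stated power looks too high once the conversion is made.

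The 83% is the only printed justification for 189 patients, and a null result will be judged by it. The Discussion already considers why IHT might fail to separate from placebo. It names a wrong remedy and short follow-up, but not low power. The power is also stated for the omnibus test alone, while the primary aim is answered by the pairwise tests.

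**Working it through.** **Inputs** (all from Sample size calculation): difference 2.7, SD 6.0, so d = 2.7/6.0 = 0.45; k = 3 equal groups; α = 0.05; 63 per group including 10% drop-out. Completers: 63 × 0.9 = 56.7, taken as 57 per group (N = 171). With no loss, N = 189.

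**Step 1: convert the range to f.** With the largest difference fixed at 0.45 SD, the position of the third mean bounds f:
- third mean equal to an extreme (for example both active arms equal): f = 0.45 × √2/3 = 0.212
- third mean midway: f = 0.45 × √(1/6) = 0.184

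**Step 2: try to reproduce 83% on the F-test.** Power = P(F > critical value), where F is noncentral with 2 and N − 3 df and λ = f²N.

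| f | 57 per group | 63 per group |
|---|---|---|
| 0.184 (third arm midway) | 55.8% (λ = 5.77) | 60.5% (λ = 6.38) |
| 0.212 (both active arms equal) | 69.1% (λ = 7.70) | 73.8% (λ = 8.51) |

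The plan's figure is not reproduced. The best case is 83 − 73.8 = 9.2 percentage points short. Reaching 83% at d = 0.45 would take 78 (f = 0.212) to 104 (f = 0.184) completers per group.

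**Step 3: what would give 83%.**
- Entering 0.45 directly as f gives over 99.9%.
- Using f = d/2 = 0.225 gives 74.5% (57 per group) or 79.0% (63 per group).
- Using f = 0.25 gives 83.5% with 57 per group. That is the smallest n to reach 83% (56 gives 82.8%), and 57 × 1.1 = 62.7 rounds up to 63.

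Solving for exactly 83% at N = 171 gives f = 0.248. As a difference this is 0.248 × (3/√2) × 6.0 ≈ 3.2 points if two arms are equal, or 0.248 × √6 × 6.0 ≈ 3.7 points if the third is midway. Neither is 2.7.

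**Step 4: the pairwise comparisons.** Three comparisons give α = 0.05/3 = 0.0167, two-sided. I used a noncentral t with the pooled error df (3n − 3) and noncentrality d√(n/2).
- n = 57: 0.45 × √28.5 = 2.40, power 49.5%
- n = 63: 0.45 × √31.5 = 2.53, power 54.5%

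Requiring a significant F-test first changes these little (about 49% and 54% by simulation). With 57 per group, 83% power needs about 3.8 points. At 2.7 points it needs about 112 completers per group.

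**Step 5: precision of fluoxetine versus placebo.** With SD 6.0 and 57 per group, the standard error is 6.0 × √(2/57) = 1.12. The unadjusted 95% half-width is 1.97 × 1.12 ≈ 2.2 points (2.1 with 63 per group). An observed difference of 1.8 would have an interval of about −0.4 to 4.0, which contains both 0 and 3.

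**The case against.** Several points can be made for the plan.

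- **The low figure is a worst case.** The text assumes that active treatment beats placebo by 2.7 points, and there are two active arms, so f = 0.212 is the natural reading. All randomised patients stay in the analysis population, so 63 per group is arguable. Both points stand. The fair headline is 69–74%, with 56–60% as the worst case. None of these reaches 83%.
- **Other routes come near 83%.** A repeated-measures between-group F-test with f = 0.212, 57 per group, two visits and an assumed correlation of 0.5 gives 81.9%. Pooled active arms against placebo with 63 per group gives 82.7%. An α of 0.10 with f = 0.212 and 63 per group gives 83.1%. Each conflicts with the text, which states a one-way ANOVA, three groups, 5% α and a drop-out allowance, and gives no correlation. They do not rescue the figure. They do show that its origin is unknown, so a reader who infers that f = 0.25 was entered goes further than the document allows.
- **Sizing on the omnibus test is a design choice.** The 83% is claimed for the F-test only. A reader might take the roughly 50% pairwise power as a second arithmetic error, or apply it to all three comparisons. The document supports neither. It is a mismatch between sizing and aim, and it covers only the active-placebo pairs.
- **The fluoxetine statement is Discussion text with no power claim.** True, so it is a secondary point about wording.

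An unseen analysis plan or full protocol is no answer. The article prints a complete calculation, and its result disagrees with its inputs.

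**Conclusion.** The power statement is wrong as written. With a largest difference of 0.45 SD, a three-group F-test at 5% has about 69% power (57 per group) to 74% (63 per group) if both active arms are equal, and about 56% to 60% if the third arm is midway. The stated 83% is consistent with a difference of about 3.2–3.7 points at 57 per group, but how it arose cannot be known from the document.

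Separately, the tests that answer the primary aim were not the basis of the sizing. Each Bonferroni-adjusted active-placebo comparison has about 50–54% power at 2.7 points.

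These results take 6.0 as the within-group SD, as the document defines it, equal group sizes, and the week-six difference as the target.

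**What to change.** Keep 189 patients, since recruitment is under way, and restate the Sample size calculation at 2.7 points and SD 6.0:
- F-test power of about 69–74% if both active arms are equal, and 56–60% in the worst case, for 57 to 63 analysed per group;
- about 50–54% for each Bonferroni-adjusted active-placebo comparison, with a note that none is given for IHT versus fluoxetine because no difference is assumed;
- 83% with 57 completers per group only for about 3.2–3.7 points (F-test) or 3.8 points (one Bonferroni pair).

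Interpret non-significant results against these figures. In the Discussion, replace the claim that the fluoxetine arm will detect whether its difference from placebo is as small as in meta-analyses with a commitment to report that difference and its confidence interval.

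The change is to wording only, with no extra patients. Its downside is a less favourable stated power, and it corrects the record without making the trial any better powered.

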### Data collection

Study data will be collected at baseline, at every follow-up and 15 days after the completion of the study. Data will be collected from different sources: medical records, questionnaires (HRSD, BDI, GS) and report forms where participants will write daily any adverse event.

### Data management

All data will be entered electronically on data sheets designed for the study. The original study forms will be entered and kept on file at the JMH. Participant files are to be stored in numerical order in a secure and accessible place and manner. Participant files will be maintained in storage for a period of five years after completion of the study. All forms related to the study data will be kept in locked cabinets. Access to the study data will be restricted. A complete back-up of the data will be performed every month.

### Statistical analysis

All patients under randomization will be included in the primary efficacy population (intention-to-treat population), regardless whether or not they adhered to the treatment protocol or provided complete data sets. Only patients who withdraw their consent to use their personal data will be excluded from the analysis. The flow of participants through the trial will be presented in a Consolidate Standards of Reporting Trials (CONSORT) diagram.

First, the three groups will be compared in order to verify that there are no significant differences among them at baseline to confirm they are comparable after randomization. Demographic characteristics will be summarized using means and standard deviation for continuous data (that is, age) and relative frequencies for qualitative data (that is, marital status, comorbidities). The baseline demographic characteristics among groups will be compared with the use of the chi square test or by one-way independent measures of analysis of variance (ANOVA) as required.

We will compare: (1) IHT versus placebo; (2) fluoxetine versus placebo; and (3) IHT versus fluoxetine. The main statistical analysis will compare primary and secondary outcome measurements among groups at weeks four and six. The primary outcome (change in mean HRSD score) and secondary outcomes (change in mean BDI and GS scores) among groups at baseline and weeks four and six, will be analyzed by one-way ANOVA to provide a statistical test of whether or not the means of the three groups are all equal. The statistically significant one-way ANOVA result (*P* <0.05) suggests rejecting the global null hypothesis H_0_ (that the means are the same across IHT, fluoxetine and placebo groups). The Bonferroni *post-hoc* test will be used to determine which means differ among the groups. Responder rates will be compared among the groups using the chi square test. Statistical significance will be set at *P* <0.05 level for all analysis. Missing data will be handled by sensitivity analysis.

All patients who received at least one dose of the study drugs will be considered in the safety analysis. Adverse events will be translated to Medical Dictionary for Regulatory Activities terms (MeDRa terms), quantified and compared among the groups using the chi square test. Homeopathic aggravation will be compared among the groups also using the chi square test.

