**Methods/design:**

A randomized, placebo-controlled, double-blind, double-dummy, three-arm trial with a six-week follow-up study was designed. The study will be conducted in a public research hospital in Mexico City (Juárez de México Hospital) in the outpatient service of homeopathy. One hundred eighty nine peri- and postmenopausal women diagnosed with major depression according to the Diagnostic and Statistical Manual of Mental Disorders, 4th edition (moderate to severe intensity) will be included. The primary outcome is change in the mean total score among groups on the 17-item Hamilton Rating Scale for Depression after the fourth and sixth week of treatment. Secondary outcomes are: Beck Depression Inventory change in mean score, Greene’s Scale change in mean score, response and remission rates and safety. Efficacy data will be analyzed in the intention-to-treat population. To determine differences in the primary and secondary outcomes among groups at baseline and weeks four and six, data will be analyzed by analysis of variance for independent measures with the Bonferroni *post-hoc* test.

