### Outcomes

The primary efficacy outcome is the change from baseline in mean total depression score using the 17-item version of the HRSD at weeks four and six. The severity of symptoms will be assessed by a blinded investigator (clinical psychologist) from the JMH. The secondary outcomes are: change from baseline in mean total depression score using BDI (a self-reported scale) at weeks four and six; change from baseline in mean total score of GS at weeks four and six; responder rates (response rate: decrease of 50% or more from baseline score; remission rate: HRSD ≤7). The number and severity of all adverse events and homeopathic aggravations during the study period and 15 days after the final dose will be collected to determine the safety of fluoxetine and homeopathic medicines. An adverse event will be defined as any untoward medical occurrence in a subject without regard to the possibility of a causal relationship. Adverse events will be collected after participants have given consent and enrolled in the study and 15 days after study completion.

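### All randomised patients are promised a place in the primary analysis, but the stated ANOVA cannot use a missing visit and no primary missing-data method is given

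*Protocol article*

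**What the plan says.** All references are to the protocol article.

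- **Population.** The abstract states: "Efficacy data will be analyzed in the intention-to-treat population". The Statistical analysis section defines that population as everyone randomised, "regardless whether or not they adhered to the treatment protocol or provided complete data sets".
- **Permitted exclusions.** The same section adds: "Only patients who withdraw their consent to use their personal data will be excluded from the analysis". This sentence concerns the analysis itself, not only the name of the population.
- **Primary outcome.** Under Outcomes it is the "change from baseline in mean total depression score using the 17-item version of the HRSD at weeks four and six".
- **Primary method.** Under Statistical analysis the outcome "will be analyzed by one-way ANOVA". The abstract describes the same test as "analysis of variance for independent measures with the Bonferroni" procedure afterwards, so no repeated-measures term is intended.
- **Missing data.** One sentence: "Missing data will be handled by sensitivity analysis".
- **Expected loss.** Under Sample size calculation: "63 patients per group are required considering also a 10% drop-out rate".

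**The concern.** A one-way ANOVA of change at week 6 needs a week-6 score from each patient it uses. The article therefore fixes who must be analysed and then fixes a method that cannot analyse all of them unless a value is supplied for those who are missing. The sentence on missing data does not close the gap. A sensitivity analysis asks how far a result depends on the assumption behind the primary analysis, and here no such assumption is stated.

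Two things are at stake. Loss in a depression trial may depend on arm and on how the patient is doing, so an observed-case comparison can be biased for any of the three contrasts and still be reported as intention-to-treat. Information already collected is also discarded: in an independent-measures test, a patient's week-4 score adds nothing to the week-6 comparison.

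**Working it through.** **Inputs from the article.** 189 patients, 63 per group, 10% drop-out, target difference 2.7 HRSD points, standard deviation 6.0 (abstract and Sample size calculation).

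**The plan's own figure.** 3 × 63 = 189. With 10% lost, 63 × 0.9 = 56.7 per group remain, or 189 × 0.9 = 170.1 in all, so 189 − 170.1 = 18.9 patients have no final score. (The stated 83% power is not reproduced from an effect size of 0.45. A one-way F-test gives 55.8% to 74.5% at 57 per group, depending on how 0.45 is converted to Cohen's f. That is a separate matter, and nothing below rests on it.)

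**Who can be used.** Set the commitment beside the method, with no imputation:

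| Scores available after baseline | Week-4 ANOVA | Week-6 ANOVA | Commitment in the text |
|---|---|---|---|
| Weeks 4 and 6 | used | used | included |
| Week 4 only | used | not used | included |
| Week 6 only | not used | used | included |
| Neither | not used | not used | included |

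The last three rows conflict with the commitment at one visit or both. If the whole 10% lack a week-6 score, about 19 patients are left out of that comparison. At week 4 the number would be smaller to the extent that loss occurs later.

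**Possible bias (illustration, assumed inputs).** Let a share q of an arm be missing, and let those patients do g points worse than that arm's completers. The mean over all randomised is

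(1 − q) × m + q × (m − g) = m − q × g,

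where m is the completers' mean improvement. The completers' mean is therefore too favourable by q × g, and the contrast between two arms is off by q₁g₁ − q₂g₂. The article gives neither q by arm nor g.

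- Common g, drop-out of 15% against 5% (with 10% in the third arm the average stays at 10%):
  - g = 3: 0.10 × 3 = 0.30 points; 0.30 / 2.7 = 11%.
  - g = 6: 0.10 × 6 = 0.60 points; 0.60 / 2.7 = 22%.
- Common g, a gap of 5 percentage points: 0.05 × 3 = 0.15 to 0.05 × 6 = 0.30 points, or 6% to 11% of the target.
- Common g, equal drop-out: zero.
- Equal drop-out of 10%, but g = 6 in one arm and 3 in the other: 0.10 × (6 − 3) = 0.30 points. Equal loss does not by itself protect the contrast.

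**Scale.** The standard error of a two-arm difference at 57 per group is 6.0 × √(2/57) = 1.12. A bias of 0.3 to 0.6 is 0.27 to 0.53 of one standard error. Its direction depends on which arm loses more, or worse, patients.

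**The case against.** The strongest reply is that the article never says patients without a score are dropped; it says the opposite. ANOVA omits them only if nothing is imputed, and an imputation rule is the kind of detail a journal article may leave to a full protocol or analysis plan that is not shown. That the ANOVA is run separately at each visit is also inferred, although it is the natural reading of a one-way, independent-measures test at weeks four and six.

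This stands in part. A reader might infer that the plan is a completer analysis mislabelled as intention-to-treat. The text does not establish that; it follows only if no values are imputed. But the article is not merely silent. It limits exclusions, names the test, and names the handling of missing data, and the handling it names is not one that can meet the commitment.

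Other stronger readings also fail:

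- The 10% allowance does not show that those patients leave the analysis. Inflating for drop-out is ordinary under intention-to-treat, because information is lost either way.
- The 0.3 to 0.6 points are not a prediction. Both inputs are assumed, and 15% against 5% is a threefold difference in drop-out.
- Stopping treatment or lacking benefit is not the same as a missing score. The article plans to keep participants in follow-up where possible, to telephone them, and to provide rescue in every arm. This should reduce missing data but gives no rule for what remains.

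**Conclusion.** The point holds as an internal conflict. The article promises an analysis of all randomised patients, fixes a test that cannot deliver it without imputation, and offers a sensitivity analysis where a primary method is needed. Followed as written, it yields an observed-case comparison at each visit.

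The number affected, up to about 19 of 189, rests on the plan's own 10% drop-out and on no imputation. The possible bias, 11% to 22% of the target difference, rests further on the assumed gap in drop-out and the assumed shortfall. It does not show that the trial would be invalid. It is enough to matter for a target of 2.7 points, and it is cheap to prevent. This should be fixed before unblinding.

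**What to change.** Replace the separate ANOVAs with one primary method that honours the commitment. Either of these would do:

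- A likelihood-based repeated-measures model of HRSD at baseline, week 4 and week 6, with baseline as a response, arm-by-visit effects and an unstructured covariance. Every randomised patient with a baseline score then contributes, and a week-4 score informs week 6 through the correlation.
- Multiple imputation of missing HRSD scores using arm, baseline and the other visit, followed by ANCOVA adjusted for baseline HRSD.

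A mixed model limited to patients with at least one post-baseline score would not be enough. The first follow-up is at week 4, so anyone lost before then would still be omitted. Under either method such patients add little information on the contrast, and the result depends on the missing-at-random assumption, which should be stated. The three planned contrasts and their Bonferroni adjustment can stay.

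Then define the sensitivity analysis as departures from that assumption, for example delta-adjusted or reference-based imputation, with the range set in advance. State one rule for missing response and remission status that keeps all randomised patients in the denominator. Deriving status from imputed scores and counting missing as failure are both defensible, and each carries its own assumption.

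The cost is a change of wording and slightly more analysis work. No new data, visits or patients are needed, and adjusting for baseline and using both visits should add precision.

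### Change scores are compared by one-way ANOVA without the baseline score as covariate, and significance tests are used to confirm baseline comparability: a valid plan that can lose precision and a check that cannot do its job

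*Protocol article*

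**What the plan says.** The Outcomes section defines the endpoint: "The primary efficacy outcome is the change from baseline in mean total depression score" on the 17-item HRSD at weeks four and six. Change in BDI and change in GS at the same visits are secondary.

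The Statistical analysis section fixes the model. Change in all three scales "will be analyzed by one-way ANOVA to provide a statistical test of whether or not the means of the three groups are all equal", and after a significant global result a Bonferroni "test will be used to determine which means differ among the groups". The same sentence lists baseline as one of the time points at which the scale scores are compared among groups. Neither this section nor any other mentions a covariate, an ANCOVA or another adjusted model.

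The section opens with a separate step: "the three groups will be compared in order to verify that there are no significant differences among them at baseline", whose stated purpose is to confirm comparability. For this, "The baseline demographic characteristics among groups will be compared with the use of the chi square test" or by one-way ANOVA.

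Two further passages bear on the point. Under Randomization, "Participants are simple randomized in a 1:1:1 ratio using a computer-generated random allocation sequence", with no stratification stated. Under Data collection, "Study data will be collected at baseline, at every follow-up", and HRSD, BDI and GS are among the questionnaires, so the covariate is already in hand.

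**The concern.** Subtracting the baseline score is itself an adjustment, but one with the slope fixed at 1. If the true regression of the follow-up score on the baseline score has another slope, two things follow. The residual variance is larger than it need be. And when the arms differ at baseline by chance, part of that difference enters the estimated treatment effect: some of it with the opposite sign if the slope is below 1, some with the same sign if it is above 1. ANCOVA estimates the slope and avoids both.

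The plan's stated check for imbalance is a set of significance tests. Under correct randomisation the null hypothesis of such a test is true by construction, so each test is significant 5% of the time whatever the state of the trial. A non-significant result does not remove an imbalance that moves the estimate, and the plan attaches no action to a significant one. At stake are precision in a comparison planned around a 2.7-point difference, and false reassurance from the baseline tests.

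**Working it through.** The plan gives no figure on this point to reproduce. The check asks how much the fixed slope can cost.

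**Inputs from the document.** Planned difference 2.7 HRSD points, SD 6.0, effect size 0.45 (Sample size calculation). 63 per group including 10% drop-out, so 63 × 0.9 = 56.7, about 57 evaluable. Entry HRSD 14 to 24 (Eligibility criteria).

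**Assumptions, not in the document.** Baseline HRSD SD s0 = 3; follow-up HRSD SD s1 = 6; r from 0.2 to 0.5, with higher values shown for completeness; equal baseline and follow-up SDs for BDI and GS. The article does not say whether its 6.0 is the SD of the score or of the change. The variance ratio depends only on r and on s0/s1, here 0.5.

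**Formulas.**
- Variance of change: s0² + s1² − 2·r·s0·s1
- ANCOVA residual variance: s1²·(1 − r²)
- The two differ by (s0 − r·s1)², which is never negative and is zero only when the slope r·s1/s0 equals 1.

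**HRSD, s0 = 3 and s1 = 6** (change 45 − 36r; ANCOVA 36(1 − r²); slope 2r):

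| r | slope | change | ANCOVA | ratio |
|---|---|---|---|---|
| 0.2 | 0.4 | 37.80 | 34.56 | 0.914 |
| 0.3 | 0.6 | 34.20 | 32.76 | 0.958 |
| 0.4 | 0.8 | 30.60 | 30.24 | 0.988 |
| 0.5 | 1.0 | 27.00 | 27.00 | 1.000 |
| 0.6 | 1.2 | 23.40 | 23.04 | 0.985 |
| 0.7 | 1.4 | 19.80 | 18.36 | 0.927 |

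For r = 0.2 to 0.5 the reduction is about 9% falling to nil. In sample-size terms, 57 per arm with ANCOVA would be worth 57/0.914 = 62 per arm at r = 0.2, 57/0.988 = 58 at r = 0.4, and 57 at r = 0.5.

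**Power.** This step takes 6.0 as the SD of change, s0/s1 = 0.5 and 57 per arm. If both active arms differ equally from placebo, Cohen's f = 0.45·√2/3 = 0.2121. The global F-test then has 69.1% power unadjusted. With ANCOVA it has 73.3% at r = 0.2, 69.7% at r = 0.4 and 69.1% at r = 0.5. That 69.1% is not the stated 83% is a separate matter.

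**BDI and GS, equal SDs.** The ratio is s²(1 − r²) / [2s²(1 − r)] = (1 + r)/2, which is 0.60 at r = 0.2 and 0.75 at r = 0.5: a reduction of 40% to 25%.

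**Carry-over of a chance imbalance (HRSD).** The standard error of a baseline difference between two arms is 3·√(2/57) = 0.56, so its 95% range is ±1.96 × 0.56 = ±1.10 points. The change score carries (slope − 1) × imbalance. At the edge of that range, this is −0.6 × 1.10 = −0.66 points at r = 0.2, −0.22 at r = 0.4, 0 at r = 0.5 and +0.22 at r = 0.6.

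**What the baseline test would let through.** If one arm differs by D from two equal arms, F = n·D²/(3·s0²) = 57·D²/27. The 5% critical value on 2 and 168 degrees of freedom is 3.05, so the test stays non-significant up to D = √(3.05 × 27/57) = 1.20 points. At slopes of 0.4 to 0.8 this carries 0.72 to 0.24 points into the comparison. The upper value is 0.72/2.7, about 27% of the planned difference.

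**The case against.** The strongest reply is that nothing is broken. With randomised 1:1:1 allocation, ANOVA of change is unbiased over randomisation and keeps its type I error. That stands in full. A reader might infer that the primary analysis is biased or invalid, or that simple randomisation gives no protection. The document supports neither reading: randomisation protects in expectation, and only the particular imbalance that occurs is left uncorrected.

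Second, baseline is not ignored, since it enters every change score. This also stands. The fair criticism is the fixed slope, not non-use.

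Third, the entry window of 14 to 24 might be thought to force a slope below 1, so that change scores must over-correct. That does not follow. Selecting on the baseline score lowers the correlation but, under linearity, leaves the regression slope unchanged. In the model above the slope is 2r, which reaches 1 at r = 0.5 and exceeds it beyond, so the direction of the error is unknown.

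Fourth, the primary-outcome gain is small, the larger gains concern secondary scales only, and all the sizes rest on assumed SDs and correlations. This is correct. The typical carry-over is also smaller than the edge-of-range figures: one standard error of imbalance (0.56) at slopes of 0.4 to 0.8 gives 0.34 to 0.11 points.

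Finally, no analysis is made conditional on the baseline tests, so false alarms have no stated consequence. That limits the harm, but the tests still cannot serve the purpose given for them.

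**Conclusion.** The point holds as one of efficiency and of a misused check. The article fixes an unadjusted one-way ANOVA of change for HRSD, BDI and GS, nothing elsewhere adjusts for the baseline score, and non-significant baseline tests are given a role that they cannot fill.

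For HRSD the precision forgone is modest and may be nil over r = 0.2 to 0.5. It would not by itself restore the trial's power, and the document does not support presenting it as a large loss on the primary outcome. For BDI and GS it could be substantial if the two SDs are about equal, which the document neither states nor excludes. The protection against a chance HRSD imbalance likewise depends on how far the slope is from 1. Since ANCOVA is never materially worse and the covariate is already collected, the change is worth making even at the low end of these ranges.

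**What to change.** Before unblinding, pre-specify an ANCOVA at each of weeks four and six for HRSD, BDI and GS, with treatment group as factor and the baseline value of the same scale as covariate. Take both the global three-group test and the Bonferroni-adjusted pairwise contrasts from that model. The outcome may stay as change from baseline: once baseline is a covariate, the estimated treatment difference is the same for change and for the follow-up score.

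Keep the baseline table, but describe the groups without significance tests. Delete the aim of confirming comparability by testing, and drop baseline from the time points at which the scale scores are compared by ANOVA.

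The cost is a few sentences in the analysis section and one error degree of freedom (167 instead of 168 with 57 per arm). No new data or visit is needed. Timing matters: an adjustment added after an imbalance has been seen would look data-driven.
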